## Abstract

**Background:**

Despite the availability of treatment options, help-seeking rates among individuals with gambling problems remain low. To reach a broader population of those affected by disordered gambling, online and self-guided interventions have been developed. Personalized normative feedback (PNF) is one of the most widely used strategies for preventing gambling issues among young adults. However, most studies on PNF efficacy focus solely on its impact on the intensity and severity of gambling behavior, without exploring its potential to increase intention to change and help-seeking behaviors. Furthermore, there is a lack of studies assessing the efficacy of PNF in addressing emerging online gambling-like behaviors, such as betting within video games or excessive financial trading of high-risk assets (eg, cryptocurrencies), which have been linked to gambling disorder.

**Objective:**

This study aims to (1) quantify intention to change and the prevalence of help-seeking behaviors in young adults in Spain with disordered gambling or trading behaviors and (2) assess the efficacy of online PNF in increasing these behaviors.

**Methods:**

A randomized controlled trial using a Solomon 3-group design was conducted with a sample of emerging adults aged 18 to 34 years. The study included 3 assessments: a pretest, an immediate posttest, and a 12-week follow-up assessment. Participants were randomized into 1 of 3 conditions, with the intervention group receiving online PNF. The primary outcomes were intention to change and help-seeking behaviors. Secondary outcomes included gambling and trading behaviors (intensity, frequency, and severity) and their longitudinal trajectories. Individual, interpersonal, and contextual factors will be assessed to identify the profile of individuals most likely to benefit from this intervention.

**Results:**

The study was funded in December 2023 by the Spanish Ministry of Social Rights, Consumer Affairs and 2030 Agenda (SUBV23/00004) and approved by the Ethics Committee of the Miguel Hernández University. The first study assessment was conducted between December 2024 and January 2025. A total of 1889 people completed the eligibility assessment, of whom 1112 (58.9%) met the inclusion criteria (gambling or trading within the past 60 days) and were enrolled in the trial. The 12-week follow-up was finalized in March 2025, with 666 completing the final assessment (59.9% retention). Data collection has been completed, statistical analyses are ongoing, and primary results are expected to be published in March 2026.

**Conclusions:**

By examining motivational outcomes rather than behavioral change alone, this trial addresses a key gap in the literature on digital interventions for gambling-related harm. Findings are expected to inform the development of scalable prevention and early intervention strategies targeting gambling and gambling-like behaviors in young adults.

## Introduction

### Background

The digitalization of gambling markets has substantially transformed the gambling landscape, contributing to increased participation in online gambling and heightened exposure to gambling-related harms [1,2]. A recent systematic review and meta-analysis of representative samples across 68 countries found that 46.2% of adults gambled in the past 12 months, with 8.7% engaging in any risky gambling behavior, and that the prevalence of problem gambling was the highest among individuals participating in online casino or slot machine gambling (15.8%) [3]. In Spain, online gambling participation has tripled since 2013, and the prevalence of problem gambling among individuals who gamble online is also markedly higher than among those who gamble exclusively offline (18.4% and 4.3%, respectively) [4]. These patterns are particularly pronounced among young adults, an age group characterized by high exposure to digital environments and increased vulnerability to addictive behaviors [1,4-6].

Beyond traditional gambling products, digitalization has facilitated the expansion of gambling-like products that encourage monetary spending across multiple online contexts [2,6-9]. Within digital environments, gambling-like practices have been most extensively studied in the context of video games. In particular, loot boxes, mechanisms that involve spending real money on randomized virtual items or rewards, have been consistently associated with increased gambling severity and gambling-related harms among adolescents and young adults [10-14]. More recently, attention has also been drawn to skin gambling, which involves wagering of in-game items with real-world monetary value and has been suggested in recent studies to have stronger associations with gambling severity than loot boxes [6,15,16].

While younger adolescents (11‐14 years) represent the largest group of video game users, recent European data indicate that the greatest growth in gaming participation has occurred among individuals aged 25 to 34 years, underscoring the relevance of this age group for research on gambling-like digital spending [17].

In parallel, this same cohort has become increasingly active on online platforms and mobile apps that allow speculative trading of financial assets, such as cryptocurrencies and other high-risk instruments [7,18,19]. Unlike traditional long-term investing, speculative trading is characterized by short-term profit seeking, frequent transactions, and exposure to highly volatile markets, features that closely resemble those of gambling activities [9,20-23]. Moreover, trading platforms often incorporate *gamblified* design elements, such as frequent push notifications or visual cues emphasizing gains, which may reinforce risky decision-making and promote these activities as a form of entertainment [24-28].

An accumulating body of research indicates that speculative trading is associated with problem gambling, impulsivity, gambling-related cognitive distortions, and other established risk factors for gambling disorder [23,29-35]. Evidence also suggests a substantial overlap between gambling and trading behaviors. Previous studies have found that a large proportion of regular gamblers engage in financial trading, and that problem gambling severity is the strongest predictor of intense and maladaptive trading behaviors [32,34-36]. Importantly, rather than the use of specific financial instruments alone, the combination of speculative trading with multiple forms of gambling, particularly in online contexts, appears to identify subgroups with elevated risk profiles and greater gambling-related harm [23].

Despite this growing evidence base, gambling and trading behaviors are rarely examined jointly within intervention research, and trading is typically not systematically considered within prevention and treatment frameworks targeting gambling-related harms. A further challenge in addressing gambling-related problems is the extremely low rate of help seeking among affected individuals. A recent meta-analysis estimated that only 0.25% of people with gambling problems have ever sought formal help, a pattern observed consistently across types of gambling, countries, and treatment formats [37]. Available Spanish data on help seeking are largely derived from clinical samples already receiving specialized treatment and may therefore underestimate unmet need in the general population [38]. Commonly reported barriers to treatment include low motivation for change, stigma, and a preference for self-managing gambling-related difficulties [39-41]. These barriers are especially relevant for young adults, who are less likely to access traditional treatment services despite experiencing elevated levels of gambling-related risk [42-44].

To overcome these limitations, internet-based and self-guided interventions have been increasingly developed to reach individuals who are not in contact with specialized services [45-48]. Personalized normative feedback (PNF) is one of the most widely studied brief motivational interventions in this context, and it constitutes the main type of intervention used in the prevention of problem gambling among young adults [5]. As a core component of motivational interviewing approaches, PNF provides individualized feedback that compares an individual’s behavior with the observed behavior of a relevant reference group, such as peers, with the aim of highlighting discrepancies, fostering self-reflection, and supporting motivation to make informed decisions about problematic behavior [49].

Although meta-analytic evidence indicates that PNF produces only small reductions in gambling frequency and severity, these modest behavioral effects suggest that its primary utility may lie in enhancing motivation to change and promoting help seeking, rather than serving as a stand-alone behavioral intervention [50]. However, most existing PNF studies have focused on behavioral outcomes, with comparatively little attention to motivational end points such as intention to change or engagement with support resources. Moreover, PNF interventions have rarely been examined in relation to emerging gambling-like behaviors, including speculative trading or other forms of digital monetary spending. This gap is particularly relevant given that cryptocurrency trading is increasingly reported in gambling helpline contacts [51], underscoring the need for low-threshold interventions capable of addressing this broader risk landscape.

### Aims of the Project

The objective of this project was 2-fold: (1) to explore intention to change and help-seeking behavior among young adults with gambling and/or trading problems, given the heightened vulnerability of this age group [5,6], and (2) to evaluate the efficacy of an online PNF intervention in increasing intention to change and help-seeking behaviors in this population. As a secondary objective, the study examined whether exposure to PNF was associated with changes in gambling and trading behaviors (eg, frequency and intensity) over the follow-up period. Finally, the study compared the effects of PNF between individuals who engage in gambling or trading without meeting the criteria for a disorder (selective prevention) and those meeting the criteria for a gambling or trading disorder (indicated prevention).

## Methods

### Ethical Considerations

The study procedures were conducted in accordance with the Declaration of Helsinki and were approved by the Committee of Research and Ethics of the Miguel Hernández University of Elche (DPS.ACC.150523). All participants provided informed consent before participation. Data were collected through a secure web-based platform and were provided to the research team in anonymized form by the panel provider, with no access to personally identifiable information, thereby ensuring participant privacy and confidentiality. Participants received nonmonetary incentives in the form of redeemable points, in accordance with the panel provider’s standard procedures. The study protocol was prospectively registered in ClinicalTrials.gov (NCT06681103) on November 7, 2024, before participant enrollment.

### Study Design

This study was designed in accordance with SPIRIT (Standard Protocol Items: Recommendations for Interventional Trials) guidelines for clinical trial protocols (refer to the SPIRIT checklist in Checklist 1). A randomized controlled trial based on an adapted Solomon 3-group design was conducted, consisting of 2 control groups and 1 intervention condition. This design structure allows for the independent assessment of the immediate effects of the intervention on the primary motivational outcomes (ie, intention to change and help-seeking behaviors) while controlling for potential pretest sensitization (testing effects).

The study included a pretest, an immediate posttest (administered directly after the intervention or initial assessment where applicable), and a 12-week follow-up assessment to evaluate the maintenance of effects 3 months after the intervention. Although the classic Solomon design includes a fourth group that receives the intervention without a pretest [52], a pretest assessment is technically required in this study to generate the PNF for each participant. Accordingly, the adaptation proposed by Moreira et al [53] for studies applying PNF was adopted, omitting the intervention group with only a posttest.

Within the single intervention group (PNF), participants were randomly assigned to 1 of 2 predefined feedback assessment sequences (PNF-A vs PNF-B). Both subgroups received identical PNF content and completed the same primary and secondary outcome measures. The distinct feature between PNF-A and PNF-B lay in the timing of the postintervention assessment of gambling and trading behaviors (ie, frequency and intensity). In PNF-A, all posttest measures were completed after receiving PNF, whereas in PNF-B, participants completed posttest assessment of gambling and trading behaviors before receiving PNF and subsequently completed the posttest assessment of primary motivational outcomes after PNF.

This sequencing was intended to support secondary analyses examining potential reporting reactivity (eg, social desirability) in self-reported behavioral outcomes [54] and involved no alteration to the interventions’ delivery, content, or the assessment of the primary outcomes.

Accordingly, the study comprised three experimental conditions, with an additional within-intervention assessment sequencing: (1) a control group with pretest and posttest assessments (assessment group); (2) a control group with posttest assessment only (delayed assessment group); and (3) an intervention group receiving PNF, with pretest and posttest assessments and randomized assessment sequencing (PNF-A vs PNF-B; Figure 1).

**Figure 1. F1:**
[figure not shown]
Flowchart of the adapted Solomon 3-group randomized controlled trial design, illustrating the assessment sequence across groups, including the intervention condition with randomized assessment sequencing (personalized normative feedback [PNF]-A and PNF-B). O1–O11 indicate assessment time points, and X denotes the intervention (PNF).

Participant allocation to each condition was conducted via a computer-generated allocation algorithm integrated into the online survey platform. To ensure equal sizes across the 4 arms, the algorithm used a least-fill dynamic allocation method. This procedure automatically assigned each incoming participant to the experimental condition with the fewest enrolled participants at the time of entry, ensuring a balanced distribution of total participants across groups independent of baseline characteristics. In cases where 2 or more conditions had the same lowest number of participants, allocation was determined by simple random selection among those conditions.

### Sample Size Estimation

Given the lack of prior studies examining the impact of online PNF on intention to change and help seeking among individuals with gambling or trading problems, sample size estimation was based on previous trials evaluating PNF effects on gambling-related outcomes in young adults. Assuming an α error of 5%, an effect size f=0.15, and a correlation between baseline and follow-up measures of 0.5 [39,57], it was estimated that a total of 164 participants would be required to achieve a statistical power (1–β) of 90% for detecting differences within and between groups on a single outcome.

Given the evaluation of multiple outcomes, a minimum effective sample size of 328 was required. To account for potential attrition, the effective sample was adjusted using the following formula: final sample size=effective sample size/(1–loss to follow-up rate). Given the online panel setting, a conservative loss-to-follow-up rate of 50% was assumed before study launch. This adjustment yielded a target enrollment of 656 participants in total, corresponding to a minimum of 164 (25%) participants per randomized condition at baseline.

### Blinding

A double-blind design was used, wherein participants were unaware of their assigned experimental condition and were blinded to the study hypotheses regarding the efficacy of the intervention. In accordance with recommendations by Boutron et al [58], the outcome evaluation was conducted with researchers blinded to allocation to minimize the risk of detection bias.

### Intervention

The online PNF intervention provided participants with a brief report summarizing the results of their baseline assessment. This PNF included (1) an overview of the gambling and trading activities in which the participant engaged, including frequency of engagement and amounts spent; and (2) assessment scores on disordered trading (Trading Disorder Scale) and gambling (Problem Gambling Severity Index), along with interpretative information indicating levels of severity. Each result was accompanied by graphical representations, allowing participants to compare their scores with population-based norms from the Spanish demographic of the same sex and age group [3].

To mitigate the potential for increased gambling or trading behaviors in individuals whose current engagement levels are below the normative average, we incorporated the recommendations put forth by Newall et al [59] by presenting the normative data in conjunction with extreme values and relevant percentages.

### Eligibility Assessment

The eligibility assessment was conducted at baseline and included sociodemographic information such as sex, age, education, employment status, and monthly income. Psychological distress was assessed using the Kessler Psychological Distress Scale [60], which measures symptoms of nervousness, hopelessness, depression, and feelings of worthlessness over the past 4 weeks. A single item assessed current or past psychiatric or psychological treatment. Suicidal behavior was evaluated using the 5-item Paykel Suicide Scale [61] in its Spanish version [62], capturing death thoughts, ideation, and suicide attempts in the past year.

Substance use indicators were collected using items adapted from the Encuesta sobre Alcohol y otras Drogas en España (EDADES) survey [63]. Alcohol risk consumption was assessed using the 3-item version of the Alcohol Use Disorders Identification Test–Consumption [64]. Gambling and trading activities during the past 60 days were identified via ad hoc items based on the EDADES survey [63], capturing engagement in traditional gambling formats (eg, bingo, lotteries, and casino), emerging gambling-like activities (eg, buying loot boxes, e-sports betting, and skin betting), and speculative trading (eg, cryptocurrency trading, foreign exchange, and commodities).

### Primary Outcomes

Intention to change gambling or trading behavior was assessed through 3 ad hoc items. Participants answered a dichotomous item (yes or no) adapted to their chosen behaviors during the screening phase (eg, “In the last year, have you thought about reducing or quitting [financial asset trading/gambling]?”). Participants then reported the likelihood of engaging in gambling or trading over the next 12 months on a scale from 0% (very unlikely) to 100% (very likely). A third item asked participants to specify their actual plan regarding their behavior (not reducing or stopping, reducing or stopping in the following 6 months, and reducing or stopping in the following 30 days), with the latter 2 items administered at baseline, postintervention assessment, and follow-up.

Intention to seek treatment was also measured (at pretest, posttest, and at 12-week follow-up) using a likelihood item (0%‐100%). Help-seeking behaviors were additionally assessed at baseline using a question adapted from the study by Rodda et al [65] about prior help seeking (eg, “Have you ever sought professional help or advice, support from family or friends, or taken any self-directed actions to reduce your [gambling/trading] behavior?”). If answered affirmatively, participants completed an adaptation of the Help-Seeking Questionnaire [65], which includes items assessing self-directed, distance-based, and face-to-face help-seeking behaviors (eg, reading forums, browsing informational websites, and talking to a gambling counselor).

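### Help-seeking behaviour is named as a primary outcome that PNF should increase, but its measure is described only as a lifetime question at baseline; the help-related effect that can be tested is on intention to seek treatment

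*Protocol article*

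**What the plan says.** The Abstract (Methods) states: "The primary outcomes were intention to change and help-seeking behaviors". The second aim in Aims of the Project is "to evaluate the efficacy of an online PNF intervention in increasing intention to change and help-seeking behaviors in this population". Study Design says that the adapted Solomon design allows assessment of "immediate effects of the intervention on the primary motivational outcomes (ie, intention to change and help-seeking behaviors". The Abstract (Objective) and the Discussion repeat the efficacy claim.

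The Primary Outcomes section sets out the measurement. Intention to change has three items, "with the latter 2 items administered at baseline, postintervention assessment, and follow-up". Intention to seek treatment is a 0-100% likelihood, given at pretest, posttest and 12 weeks. On behaviour the text reads "Help-seeking behaviors were additionally assessed at baseline using a question adapted from" an earlier study, and the example item begins "Have you ever sought professional help or advice, support from family or friends, or taken any self-directed actions". The detailed instrument depends on that answer: "If answered affirmatively, participants completed an adaptation of the Help-Seeking Questionnaire". No posttest or 12-week administration is given for either part of the behaviour measure.

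**The concern.** A lifetime question answered before PNF cannot be changed by PNF. Followed as written, the plan names a behaviour as a primary efficacy outcome and then observes no instance of it after the intervention.

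What is at stake is the label on the result. If the 0-100% item shifts, the natural report under the present wording is that PNF increased help-seeking behaviours, although participants only rated how likely they were to seek treatment. The Primary Outcomes section itself treats the two as separate constructs. The Discussion presents this efficacy question as one of the trial's main novelties, so the label carries weight.

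**Working it through.** **1. Time points side by side**

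| Measure | Section | Time points stated | Window | Can it respond to PNF? |
|---|---|---|---|---|
| Thought of cutting down or quitting (yes/no) | Primary Outcomes | not among the repeated items | last year | no, if asked before PNF |
| Likelihood of gambling or trading (0-100%) | Primary Outcomes | baseline, post-intervention, follow-up | next 12 months | yes |
| Plan to reduce or stop (3 categories) | Primary Outcomes | baseline, post-intervention, follow-up | next 30 days or 6 months | yes |
| Intention to seek treatment (0-100%) | Primary Outcomes | pretest, posttest, 12 weeks | not stated | yes |
| Prior help seeking, then Help-Seeking Questionnaire if yes | Primary Outcomes | baseline | ever | no |
| Gambling and trading frequency and intensity | Secondary Outcomes | baseline, posttest, follow-up | past year, then previous 3 months at follow-up | yes, at follow-up |
| Gambling Disorder Identification Test | Secondary Outcomes | follow-up | not stated | taken after PNF |

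The article gives later time points wherever it describes a later measurement, and it shortens the recall window at follow-up for gambling and trading. Against that pattern, the baseline time point for help-seeking behaviour reads as a statement of the schedule and not as a detail left out.

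**2. Would other time points help?**

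- *Immediate posttest.* Study Design places it directly after the intervention, or after the initial assessment where that applies. No time has passed in which a participant could seek help, so an immediate effect on behaviour could not be seen there. An immediate effect on intention could.
- *12 weeks, with the lifetime item unchanged.* Anyone who had sought help before enrolment should answer yes again, so old and new help seeking are mixed. In arms with a pretest, new help seeking could be read from those who first answered no. The delayed assessment group has no pretest, and the article does not say when, or whether, that arm receives the item.
- *12 weeks, with a window since baseline.* This would measure the behaviour that the second aim is about. The article does not describe such an item.

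**3. The sample size calculation**

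Inputs from Sample Size Estimation: alpha 0.05, f = 0.15, correlation rho = 0.5 between baseline and follow-up, power 90%. Assumed, because the article does not state them: g = 4 arms, m = 2 measurements, and a within-between interaction in a repeated-measures ANOVA.

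- Noncentrality: f² × N × m / (1 − rho) = 0.0225 × 164 × 2 / 0.5 = 14.76.
- df1 = (g − 1)(m − 1) = 3; df2 = (N − g)(m − 1) = 160.
- Power = 0.905, so the stated 164 is reproduced. With g = 3 and m = 2 the result is 144; with g = 4 and m = 3 it is 136.
- Multiple outcomes: 2 × 164 = 328. Attrition: 328 / (1 − 0.5) = 656. Per arm: 656 / 4 = 164.

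The figures are consistent with each other, but they presuppose an outcome measured at baseline and again later. For a measure taken once, m = 1 and df1 = 3 × 0 = 0: there is no interaction to test. The calculation therefore does not apply to help-seeking behaviour as described, and a larger N would not change this. Arms can differ on a pre-intervention lifetime item only by chance.

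**The case against.** The strongest reply is that the article never says that behaviour was recorded *only* at baseline. It says that it was *additionally* assessed then. Study Design refers to a posttest of the primary motivational outcomes after PNF, and lists help-seeking behaviours among those outcomes. The flowchart of assessments is not shown, the article condenses a longer protocol, and *baseline* is used loosely, since the eligibility screen is also placed there. This stands in part. Baseline-only measurement is a strong inference from the pattern of stated time points, not the article's own wording. What remains is that the sections conflict and the described schedule does not deliver the stated efficacy outcome.

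A second reply is that the help-seeking domain is measured after PNF through intention to seek treatment, and that the Abstract (Conclusions) stresses motivational outcomes. This also stands. A reader might infer that half of the primary efficacy question has no post-intervention data, or that none of the 1112 enrolled participants has a usable help-seeking value. The article supports neither. Intention to seek treatment is repeated at three time points and can be tested; the gap is confined to behaviour. Nor is 1112 a suitable denominator: new behaviour could appear only at 12 weeks, which 666 participants completed, and what they were asked there on this point is not described.

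A reader might also count the past-year item on thoughts of cutting down as a second defect. It is not one: it can serve the descriptive first objective, and two intention-to-change items are repeated.

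**Conclusion.** The concern holds in this form: the article claims to test an effect of PNF on help-seeking behaviour, and the measurement that it describes permits a test only on intention to seek treatment. The immediate effect on behaviour named in Study Design could not be observed at a posttest given straight after the intervention.

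In size, one help-related measure is described after PNF, and it measures intention. None is described that measures behaviour. No power or sample-size figure changes. The first objective, the prevalence of help seeking, is served by the baseline item.

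The conclusion rests on taking the Primary Outcomes section at its word. If the 12-week questionnaire did carry behaviour items, the fault is one of reporting, and whether the aim can be met then depends on their recall window.

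**What to change.** Data collection is complete and the trial was prospectively registered, so establish the facts before restating any outcome. Do this before results are reported:

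1. Reconcile the Abstract, Aims of the Project, Study Design, Primary Outcomes and Discussion against the instruments actually given in each arm and the registered outcomes. State the time points and recall window of the help-seeking behaviour measure.
2. If behaviour items were given at 12 weeks, say so. Analyse new help seeking since baseline at 12 weeks only, as far as the recall window allows, and say how the arm without a pretest is handled.
3. If they were not, name intention to seek treatment and the two repeated intention-to-change items as the primary efficacy outcomes. Report the change of outcome label openly, keep lifetime help seeking as descriptive for the first objective, and drop the efficacy claim for help-seeking behaviours.

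The cost is a check of the questionnaires and the registration, changes of wording and, under step 3, a narrower headline claim. No new data are needed.
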